### Design and randomization

The 222 village clusters were randomized to intervention or control clusters stratified by region and access to health services. We defined health service access as vaccination coverage by 12 months of age assessed among children aged 12–23 months [24], using BHP HDSS data from 2015 to 2016. This pre-trial vaccination coverage was based on Bacillus Calmette Guerin (BCG) vaccine, three doses of OPV, three doses of Pentavalent (diphtheria, tetanus, pertussis, hepatitis B, haemophilus influenza type B), and MV. We defined low and high pre-trial vaccination coverage using the median as a cut-off point. Within each of the two coverage strata per region, we assigned one half of the clusters to receive intervention and health check-up, and the other half to receive only health check-up, based on an externally generated random number.

### Study population

Children living in BHP’s rural HDSS are eligible to enter RECAMP-MV if 9–59 months of age and RECAMP-OPV if 0–8 months of age. A child is excluded if it: 1) is considered overtly ill by the enrolling nurse or 2) has an axillary temperature > 39 °C or 3) is aged > 6 months and has a mid-upper-arm-circumference < 110 mm or 4) has experienced an allergic reaction after a prior vaccination or 5) is followed in another ongoing BHP trial in rural Guinea-Bissau (i.e. children from RECAMP-OPV will not be enrolled into RECAMP-MV once they turn 9 months old, and children who are < 2 months old and enrolled in a randomized trial giving BCG and OPV at a home visit shortly after birth [25] will not be enrolled into RECAMP-OPV). Criteria 1–4 ensure that we avoid enrolment of severely acutely ill or immunocompromised children, and these criteria are based on WHO recommendations [10, 11], which we have translated into local practice. Criteria 5 is set to avoid data interpretative issues.

### Intervention

RECAMP-MV: We offer one dose of a WHO pre-qualified monovalent live attenuated measles vaccine (Edmonston-Zagreb strain from Serum Institute of India) to children aged 9–59 months in intervention clusters.

RECAMP-OPV: We offer one dose of a WHO prequalified standard bivalent OPV to children aged 0–8 months in intervention clusters. To mimic the way most OPV campaigns are implemented, we initiated the RECAMP-OPV trial with two visits one month apart where logistically feasible. At the second visit, a second dose of OPV is offered to children in intervention clusters, while children in both control and intervention clusters are health examined and weighed.

The cold chain for both vaccines is documented. We provide the MV and OPV campaign vaccinations independently from Guinea-Bissau’s routine child vaccination program [26] (Fig. 1).

**Fig. 1 Fig1:**
[figure not shown]
Guinea-Bissau’s routine child vaccination program

### Blinding

It is common practice in Guinea-Bissau that when a mother/guardian visits the health system with a sick child, the mother/guardian brings the child’s vaccination card; it could be speculated that health system personnel give low treatment priority to children with high vaccination coverage and vice versa. Thus, to avoid the risk of differential treatment decision by health system personnel, we do not register cluster assignment on the children’s vaccination cards.

### Sample size considerations

RECAMP-MV: Children are followed from enrolment and until eligibility for a national MV campaign. We aim to have minimum 80% power to detect at least a 30% reduction in non-accidental mortality or non-accidental morbidity (composite outcome) given that this is the true reduction during an average follow-up period of 18 months. The planned sample size was originally based on 182 clusters and a composite outcome rate of 20/1000 person-years among children aged 9–59 months in BHP’s rural HDSS. Based on Hayes and Moulton’s power formula for a cluster-randomized trial [27], our initial power calculations indicated 86% power to detect at least a 30% reduction if we enrolled 14,500 children (with a between cluster variation coefficient of 0.25 and a harmonic mean (reciprocal of the arithmetic means of the reciprocals) of total projected accumulated observation time per cluster of 107 person-years at risk). After discussions with our data safety and monitoring board we decided to re-evaluate the power calculations for both trials when more information on outcome rates and distribution of enrolments between the clusters was gained, to verify total enrolments needed. This re-evaluation was based on data from the first complete round of enrolment and follow-up visit. As Table 2 shows for RECAMP-MV, we observed a lower composite outcome rate and harmonic mean of total projected accumulated observation time per cluster, than expected. Our data safety and monitoring board supported our decision to enlarge the number of clusters from 182 to 222. This increased the planned enrolments from 14,500 to 18,000 children which gives us 80% power to detect a 30% reduction in the composite outcome (with an assumed control cluster outcome rate of 17/1000 person-years at risk and a harmonic mean of total projected accumulated observation time per cluster of 84 person-years at risk).

**Table 2 Tab2:** Sample size estimates derived from the first complete round of enrolment and follow-up visit of RECAMP-MV and RECAMP-OPV

RECAMP	MV	OPV
Number of clusters	222	
Alpha	0.05	
Between cluster variation coefficient	0.25	
Number of eligible children to be enrolled	18,000	10,000
Observed non-accidental deaths/non-accidental hospitalizations rates	15/1000 pyrs*	48/1000 pyrs**
Harmonic mean of total projected accumulated observation time per cluster	84 pyrs	40 pyrs
Expected reduction	30%	25%
*Power*	*80%*	*80%*

*Assuming that our observed composite outcome rate (15/1000 pyrs) is an average of the rates in our control and intervention clusters, and that the real difference between the clusters is 30%, we assumed the rates to be 17/1000 pyrs in control clusters and 12/1000 pyrs in intervention clusters when re-evaluating our power calculations

**Assuming that our observed composite outcome rate (48/1000 pyrs) is an average of the rates in our control and intervention clusters, and that the real difference between the clusters is 25%, we assumed the rates to be 55/1000 pyrs in control clusters and 41/1000 pyrs in intervention clusters when re-evaluating our power calculations

*Abbreviation*: Pyrs = person-years at risk

RECAMP-OPV: Children are followed from enrolment and until eligibility for any national vaccination campaign or for a maximum of 12 months. We aim to have minimum 80% power to detect at least a 25% reduction in non-accidental mortality or non-accidental morbidity (composite outcome) given that this is the true reduction during an average follow-up period of 10 months. The planned sample size was originally based on 182 clusters and a composite outcome rate of 70/1000 person-years among children aged 0–8 months in BHP’s rural HDSS. Based on Hayes and Moulton’s power formula for a cluster-randomized trial [27], our initial power calculations indicated 80% power to detect at least a 25% reduction if we enrolled 6500 children (with a between cluster variation coefficient of 0.25 and a harmonic mean (reciprocal of the arithmetic means of the reciprocals) of total projected accumulated observation time per cluster of 40 person-years at risk). After the re-evaluation we observed a lower composite outcome rate than expected. We enlarged the number of clusters from 182 to 222 and increased the planned number of enrolments from 6500 to 10,000 children which gives us 80% power to detect a 25% reduction in the composite outcome (with an assumed control cluster outcome rate of 55/1000 person-years at risk and a harmonic mean of total projected accumulated observation time per cluster of 40 person-years at risk).

Table 2 summarizes the final sample size calculation estimates for both trials.

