**Methods:**

Both trials are cluster-randomized trials among children registered in Bandim Health Project’s rural health and demographic surveillance system throughout Guinea-Bissau. RECAMP-MV is conducted among children aged 9–59 months and RECAMP-OPV is conducted among children aged 0–8 months. We randomized 222 geographical clusters to intervention or control clusters. In intervention clusters, children are offered MV or OPV (according to age at enrolment) and a health check-up. In control clusters, children are offered only a health check-up. Enrolments began in November 2016 (RECAMP-MV) and March 2017 (RECAMP-OPV). We plan 18,000 enrolments for RECAMP-MV with an average follow-up period of 18 months and 10,000 enrolments for RECAMP-OPV with an average follow-up period of 10 months. Data collection is ongoing. The primary outcome in both trials is non-accidental death or non-accidental first non-fatal hospitalization with overnight stay (composite outcome). Secondary outcomes are: non-accidental death, repeated non-fatal hospitalizations with overnight stay, cause-specific primary outcome, outpatient visit, and illness. We obtained ethical approval from Guinea-Bissau and consultative approval from Denmark.

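### RECAMP-OPV: a harmonic mean of 40 person-years per cluster cannot be reconciled with 10,000 children, 222 clusters and 10 months of average follow-up; on the plan's own formula the power is at most 77–79%

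*Protocol article*

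**What the plan says.** The section on sample size considerations sets a target of at least 80% power for a 25% reduction in RECAMP-OPV, "given that this is the true reduction during an average follow-up period of 10 months". The abstract gives the same plan: "10,000 enrolments for RECAMP-OPV with an average follow-up period of 10 months". Children are followed "until eligibility for any national vaccination campaign or for a maximum of 12 months".

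The original calculation used 182 clusters and a rate of 70/1000: "our initial power calculations indicated 80% power to detect at least a 25% reduction if we enrolled 6500 children", with 40 person-years entered as the harmonic mean. After the re-evaluation, "We enlarged the number of clusters from 182 to 222 and increased the planned number of enrolments from 6500 to 10,000 children". The final power of 80% assumes a control rate of "55/1000 person-years at risk and a harmonic mean of total projected accumulated observation time per cluster of 40 person-years at risk". Table 2 repeats the 40, with a between-cluster variation coefficient of 0.25 and alpha 0.05; its footnote gives 55/1000 in control and 41/1000 in intervention clusters. Within strata, "we assigned one half of the clusters to receive intervention and health check-up". The statistical analyses section says that individual-level data will be used because cluster sizes differ.

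**The concern.** The quantity entered in the formula is the "harmonic mean of total projected accumulated observation time per cluster". It is bounded above by the arithmetic mean, which follows directly from enrolment, average follow-up and number of clusters. The value of 40 lies above that bound. The 80% power is stated for the primary outcome and was the reason for settling on 222 clusters and 10,000 children. If one of its inputs is impossible given the others, the reader cannot tell what power the design has, or whether the person-time or the follow-up was misreported.

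**Working it through.** **Inputs** (protocol article, sample size considerations, Table 2 and its footnote): 222 clusters, so c = 111 per arm; 10,000 children; 10 months average follow-up; λ0 = 0.055; λ1 = 0.041 as printed, or 0.04125 for an exact 25% reduction; k = 0.25; harmonic mean y = 40. Alpha is 0.05; two-sided is assumed, since 95% confidence intervals are planned.

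**Formula** (Hayes and Moulton, rates):

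power = Φ( √[ (c − 1)(λ0 − λ1)² / V ] − 1.96 ), with V = (λ0 + λ1)/y + k²(λ0² + λ1²).

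**1. Reproducing the stated 80%.** With y = 40 and λ1 = 0.041:
- V = 0.096/40 + 0.0625 × 0.004706 = 0.002400 + 0.000294 = 0.002694
- 110 × 0.014² / 0.002694 = 8.00; √8.00 = 2.83; 2.83 − 1.96 = 0.87; power 80.8%

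With λ1 = 0.04125 it is 79.2%. The formula was applied correctly, and 40 is the value behind the 80%.

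**2. Upper bound for y.** 10,000 × (10/12) / 222 = 37.5 person-years per cluster. The harmonic mean equals this only if all clusters have the same person-time.

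**3. Could rounding explain it?** An average of 10.49 months, reported as 10, gives 10,000 × (10.49/12) / 222 = 39.4. Reaching 40 with equal clusters takes 40 × 222 × 12 / 10,000 = 10.66 months.

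**4. Power at the bound.** With y = 37.5 and λ1 = 0.041:
- V = 0.002557 + 0.000294 = 0.002851
- 0.02156 / 0.002851 = 7.56; √7.56 = 2.75; 2.75 − 1.96 = 0.79; power 78.5%

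With λ1 = 0.04125 it is 76.9%.

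**5. Scenario for unequal clusters.** The article gives no distribution of OPV cluster sizes. For RECAMP-MV the stated harmonic mean is 84, against an arithmetic mean of 18,000 × 1.5 / 222 = 121.6, a ratio of 0.69. If that ratio also held for OPV, y = 0.69 × 37.5 = 25.9, and the cluster-level formula gives 64% (λ1 = 0.041) or 62% (λ1 = 0.04125).

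**6. The same scenario under the planned type of analysis.** The harmonic-mean penalty belongs to a comparison of unweighted cluster rates. With person-time weighting, the Poisson term uses the arithmetic mean, and inequality of size only inflates the between-cluster term, by 1 + CV². For lognormal sizes this is 1/0.69 = 1.45. Then, with λ1 = 0.041:
- V = 0.002557 + 1.45 × 0.000294 = 0.002983
- 0.02156 / 0.002983 = 7.23; √7.23 = 2.69; power 76.7%

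With λ1 = 0.04125 it is 75.1%. Simulation of a person-time-weighted rate ratio with cluster-robust variance, as a stand-in for the Cox model, gave about 76–77% under the same assumptions.

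| y (person-years) | Basis | Power, 41 / 41.25 per 1000 |
|---|---|---|
| 40 | as stated | 80.8% / 79.2% |
| 37.5 | bound at 10 months, equal clusters | 78.5% / 76.9% |
| 25.9 | RECAMP-MV ratio, cluster-level formula | 64% / 62% |

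**7. The superseded design.** 6500 × (10/12) / 182 = 29.8, and a full 12 months for every child gives 6500 / 182 = 35.7. The 40 entered there was impossible under any permitted follow-up.

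**The case against.** The best defence is that the only loss the document establishes is about two percentage points. This is right. Step 4 is the firm result; anything lower needs a cluster-size distribution that is not reported.

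A reader might infer from step 5 that the trial has only 62–64% power and is materially underpowered. The document does not support that. The 0.69 is derived from RECAMP-MV's planning figures, not reported, and MV differs in age group, number of enrolment rounds and follow-up rule. The planned analysis is a Cox model on individual data with cluster-robust standard errors, for which step 6 shows a much smaller loss.

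A reader might also infer that 40 was simply carried over from the 182-cluster design. The value is unchanged although planned enrolment per cluster rose from 35.7 (6500/182) to 45.0 (10,000/222). But the text says that both trials were re-evaluated, and Table 2 is presented as derived from the first complete round, so carry-over remains conjecture.

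Finally, the wrong figure may be the 10 months and not the 40. With every child followed for 12 months the arithmetic mean would be 10,000/222 = 45.0, and a harmonic mean of 40 becomes possible. This stands as a possibility, but it contradicts the average stated in the abstract, the primary objectives and the sample size section. The discussion also expects national OPV campaigns to shorten follow-up.

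**Conclusion.** The inconsistency is certain: 40, 10 months, 10,000 children and 222 clusters cannot all hold, and rounding of the 10 months does not close the gap. If the 10 months is correct, power on the plan's own formula is at most 77–79%, reached only with equal clusters, and is lower because cluster sizes vary. The size of that further loss cannot be computed from the document. The 62–64% is a cluster-level scenario with a borrowed ratio; 76–77% is the corresponding simulated figure for a person-time-weighted, cluster-robust analysis with assumed lognormal sizes. Neither is an estimate of the trial's actual power. The superseded 182-cluster calculation shows that the figure of 40 is unreliable, but has no bearing on the power of the current design.

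**What to change.** Recompute the OPV harmonic mean from the first-round enrolment counts per cluster and the projected follow-up. Then do one of two things:
- If 10 months stands, replace 40 in the RECAMP-OPV sample size text and in Table 2, and restate the power or the detectable reduction.
- If 40 came from a longer projected follow-up, correct the 10-month average in the abstract, the primary objectives and the sample size section. At least 10.7 months is needed, and more with unequal clusters.

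It would help to report the arithmetic mean next to the harmonic mean. The cost is one recalculation from data already held and a change of wording; the stated power may become slightly less favourable. No extra enrolment is needed and the design does not change.

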### Enrolment and follow-up procedures

A pilot phase was initiated in Biombo from November 2016 to March 2017. We trained three field teams, each consisting of at least four field assistants and one enrolling nurse. The consent process, structured interviews during enrolment, and structured interviews during follow-up take place in Portuguese Creole managed by the field teams (interview questions are written in Portuguese and based on BHP’s rural HDSS questionnaires used in previous studies). If necessary, a villager is called to act as a translator.

For RECAMP-MV, we plan 2–3 enrolment rounds to visit children who were not home at a previous enrolment visit, or who later move into BHP’s rural HDSS area. For RECAMP-OPV more enrolment rounds are needed. The written consent process is two phased: 1) a field assistant conducts a household visit where he explains to the mother/guardian of an eligible and present child that, “In the past the Ministry of Health has provided many MV and OPV campaigns as the mother/guardian probably remembers. Now there is rarely any measles infection and no polio infection in Guinea-Bissau. Therefore, in the future, the campaigns may stop. BHP wants to know if it is good for children’s health to stop or continue MV and OPV campaigns. To know this, we will vaccinate in some but not other villages. When the work is done all children aged >9 months in the villages that do not receive vaccines today will be offered MV. If you are interested your child should be brought to our health post today”, the field assistant does not inform the mother/guardian about cluster assignment when referring to the health post. 2) at the health post an enrolling nurse/field assistant carefully explains both trials, usually to several mothers/guardians at a time. If a mother/guardian is illiterate a witness independent from the field team is called. After the explanation, any questions from the mothers/guardians are welcomed. If mothers/guardians want their children to participate they are requested to give their signatures/fingerprints on a consent form and then they receive an information letter written in Portuguese.

After consent, the enrolling nurse performs a health check-up of one child at a time (assessing illness, issues with prior vaccination, and measuring axillary temperature, mid-upper-arm-circumference, and weight). If the enrolling nurse experiences that a child is overtly ill, the child’s mother/guardian is given health advice, and if necessary offered health facility transport, irrespective of cluster assignment. Overtly ill children are offered enrolment at a subsequent visit, if recovered.

If a child is assessed healthy in intervention clusters, the child aged 9–59 months is administered a 0.5 ml reconstituted MV from a 10-dose vial by deep subcutaneous injection into the left subscapular region (leftover doses are discarded six hours after reconstitution), and the child aged 0–8 months is administered two oral drops of OPV from a multi-dose vial (leftover doses are discarded after 28 days). If a child is assessed healthy in control clusters, the child is not administered MV or OPV.

All enrolled children are followed through regular household visits by field assistants who collect information on death and hospitalization, among other. The visits are conducted every two months to children < 12 months of age in Oio, Biombo and Cacheu for logistical reasons, and every six months to older children, and in the remaining regions. If a field assistant registers the death of a child, a specially trained field assistant conducts a verbal autopsy at a subsequent visit [28]. An extra follow-up visit is conducted among a subgroup of enrolled children one-two months after enrolment; the mothers/guardians of these children are visited by field assistants to collect information on outpatient visit and maternally reported illness in the elapsed time span. This visit is also utilized to provide a second OPV dose to children aged 0–8 months in intervention clusters. Figure 2 shows the flow from eligibility to follow-up in RECAMP-MV and RECAMP-OPV.

**Fig. 2 Fig2:**
[figure not shown]
Flowchart from eligibility to follow-up in RECAMP-MV and RECAMP-OPV. Abbreviations: MV = measles vaccination; OPV = oral polio vaccination; MUAC = mid-upper-arm circumference; Y/N/U = yes/no/unknown

### Outcomes

The primary outcome for each trial is defined as a composite outcome to ensure sufficient power. It consists of:
non-accidental mortality ornon-accidental morbidity (first non-fatal hospitalization with overnight stay)

The secondary outcomes assess other health measures. They consist of:
non-accidental mortalitynon-accidental repeated morbidity (at least one non-fatal hospitalization with overnight stay)cause-specific primary outcome (malaria, diarrhea, and respiratory infections [29])proportion of non-accidental outpatient visits and non-accidental maternally reported illnesses in a sub-group 1–2 months after enrolment in the elapsed time spanFurthermore in RECAMP-OPV: weight at the extra follow-up visit 1–2 months after enrolment

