#### Primary analysis of the primary outcome

The main conclusion in RECAMP-MV and RECAMP-OPV will be based on a per-protocol analysis. The primary outcome will be analyzed in a Cox proportional hazards model, adjusted by region, pre-trial vaccination coverage, and sex, with age as the underlying timescale. We will use cluster-robust standard errors to account for intra-cluster correlation. Children will enter the analysis on the day of enrolment, and their follow-up will be censored at:
RECAMP-MV: death due to accident, migration or eligibility for a national MV campaign, whichever comes first.RECAMP-OPV: death due to accident, migration, eligibility for any national vaccination campaign, or a maximum of 12 months of follow-up, whichever comes first.

In both trials, hospital admissions due to accidents are ignored but the follow-up time is censored while the child is admitted.

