#### Secondary outcomes

In per-protocol analyses, we will assess the secondary outcomes: non-accidental mortality, non-accidental repeated morbidity, and cause-specific primary outcome. These secondary outcomes will be analyzed in Cox proportional hazards models as described for the primary outcome. Furthermore, we will analyse outpatient visits and maternally reported illnesses occurring 1–2 months after enrolment in per-protocol analyses using log-binomial regression models adjusted for region, pre-trial vaccination coverage, and sex. In RECAMP-OPV, we will furthermore analyze weight and MUAC 1–2 months after enrolment using multiple regression models adjusted for region, pre-trial vaccination coverage, and sex.

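### The secondary outcome called repeated morbidity is defined as at least one admission, which contradicts its label, and no rule says whether or how readmissions count

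*Protocol article*

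**What the plan says.** In the protocol article, the Outcomes section gives the non-fatal part of the primary composite as non-accidental "morbidity (first non-fatal hospitalization with overnight stay"). The list of secondary outcomes that follows has non-accidental "repeated morbidity (at least one non-fatal hospitalization with overnight stay"). The abstract (Methods) names the same secondary outcome "repeated non-fatal hospitalizations with overnight stay".

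The analysis section on secondary outcomes groups "non-accidental mortality, non-accidental repeated morbidity, and cause-specific primary outcome" and states: "These secondary outcomes will be analyzed in Cox proportional hazards models as described for the primary outcome". The model referred to is in the section on the primary analysis: "The primary outcome will be analyzed in a Cox proportional hazards model, adjusted by region, pre-trial vaccination coverage, and sex", with age as the time scale. It adds: "We will use cluster-robust standard errors to account for intra-cluster correlation".

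That section ends follow-up at accidental death, migration or campaign eligibility, and in RECAMP-OPV also at 12 months. It has one rule for time spent in hospital, and this covers accidental admissions only: they are not events, and the time in hospital is taken out of follow-up. Nothing comparable is said for non-accidental admissions.

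**The concern.** The label and the abstract promise an outcome about repeated admissions. The bracketed definition sets a threshold that the first admission already meets. The model is taken from an outcome whose hospitalization event is the first one, and nothing is added about return to risk after discharge.

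Three different outcomes fit the text: first admission, two or more admissions, and all admissions. If the literal definition is followed, the trial reports the hospitalization component of its primary outcome a second time, without deaths, under a label that does not fit it. If another reading is followed, the analysis departs from the published definition. The Discussion says that blinding the research group would have needed a placebo, which is not used, and the same group performs the analyses. The choice between readings should therefore be fixed in writing before results are seen.

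**Working it through.** **Step 1: the wording side by side.**

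| Place | What counts as the event |
|---|---|
| Outcomes, primary | first non-fatal overnight admission (or death) |
| Outcomes, secondary | at least one such admission |
| Abstract, Methods | repeated admissions, in the plural |
| Secondary outcomes (analysis) | same Cox model as the primary; no recurrent-event form named |

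The time at which a child has had at least one admission is the time of the first admission. The second row is therefore the first row without deaths, and it does not match the third. The fourth row does not settle the matter, because a Cox model can be fitted to first events or to repeated events.

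**Step 2: the plan's own figures.** The article gives no event count or power for this outcome. The stated 80% power concerns the primary outcome and reproduces with the Hayes and Moulton formula, c = 1 + (z_α/2 + z_β)²[(λ0+λ1)/y + k²(λ0²+λ1²)]/(λ0−λ1)², solved for power with 111 clusters per arm and k = 0.25.
- RECAMP-MV, λ0 = 0.017, λ1 = 0.7 × 0.017 = 0.0119, y = 84: √(110 × 0.0051²/0.000371) − 1.96 = 0.82, power 79.3%.
- RECAMP-OPV, λ0 = 0.055, λ1 = 0.75 × 0.055 = 0.04125, y = 40: √(110 × 0.01375²/0.002702) − 1.96 = 0.81, power 79.2%.

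Neither figure depends on how the secondary outcome is defined.

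**Step 3: how far the readings differ.** No readmission rate is given, so this is an illustration. Inputs from the abstract and Table 2 are 18,000 children, 15/1000 person-years and 18 months (MV), and 10,000 children, 48/1000 person-years and 10 months (OPV). The observed composite rate stands in for the admission rate, although it also includes deaths.

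Expected admissions per child are m = 0.015 × 1.5 = 0.0225 (MV) and m = 0.048 × 10/12 = 0.04 (OPV). Totals are 18,000 × 0.0225 = 405 and 10,000 × 0.04 = 400. With Poisson counts P(none) = e^(−m). With gamma frailty of shape θ (assumed), P(none) = (1 + m/θ)^(−θ) and P(exactly one) = m(1 + m/θ)^(−θ−1). The share of admissions lost if only the first counts is 1 − P(at least one)/m.

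| Trial, assumption | Admissions | Children with ≥1 | Children with ≥2 | Share lost |
|---|---|---|---|---|
| MV, Poisson | 405 | 400 | 4 | 1.1% |
| MV, θ = 0.1 | 405 | 362 | 38 | 10.7% |
| MV, θ = 0.05 | 405 | 331 | 57 | 18.2% |
| OPV, Poisson | 400 | 392 | 8 | 2.0% |
| OPV, θ = 0.1 | 400 | 331 | 55 | 17.3% |
| OPV, θ = 0.05 | 400 | 290 | 74 | 27.6% |

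At half the rate the Poisson shares fall to 0.6% (MV) and 1.0% (OPV).

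A simpler route assumes that a fraction q of admitted children has exactly one readmission. The share lost is then q/(1+q): 0.10/1.10 = 9% and 0.20/1.20 = 17%.

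**The case against.** The best defence is that the authors meant one or more admissions per child, all counted. The Outcomes section uses *first* for the primary and *repeated* for the secondary, and the abstract uses the plural. The section on the primary analysis never says that its Cox model stops at the first event, and hospitalization is not among its censoring events. A Cox model on the age scale with cluster-robust errors, and with risk time already interrupted for accidental admissions, is close to a recurrent-event analysis. The data analysis plans in Additional files 1 and 2 are not at hand and may settle the risk-set rule.

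Much of this stands. A reader might infer that readmissions will certainly be discarded. The documents do not support that, because the first-event form of the model is inferred from the outcome definition and stated nowhere. A reader might also infer that a planned objective on total hospitalization burden goes unmet. No such objective is stated; the Secondary objectives speak only of other health measures. Nor would a first-admission result be worthless: beside the mortality outcome, it shows which component drives the composite.

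The defence does not remove the contradiction. The article does more than leave a detail to an analysis plan: it prints a definition, and that definition does not say what the label and the abstract say. If all admissions were intended, the bracket fails to express it.

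**Conclusion.** Wrong as written, and minor. The definition of one secondary outcome contradicts its own label and the abstract, and the model carried over has no rule for repeated events. The literal result is time to first non-fatal admission; the intended one may be different.

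The size cannot be read from the documents. It is about 1-2% of admissions under Poisson counts at the observed composite rates, and more if admissions cluster within children. The 9-17% figure rests on an assumed 10-20% of admitted children with one readmission, and the frailty results rest on assumed shapes. A reader who takes a large loss of events as established goes beyond the evidence. The primary analysis, its power and the main conclusion are unaffected.

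**What to change.** Choose one definition and use it in the abstract, the outcome list and the analysis section.

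- **If all admissions are meant:** replace the at-least-one wording with *all non-accidental non-fatal overnight hospitalizations per child*. State that the Cox model is in counting-process (Andersen-Gill) form on the age scale. The child is not at risk while admitted and returns to risk after discharge, and follow-up ends at death or at the censoring events already listed. Standard errors are clustered on the village cluster, which also covers dependence between a child's own admissions, since children are nested in clusters.
- **If first admission is meant:** rename the outcome *first non-fatal hospitalization* in all three places and drop the word *repeated*.

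The cost is a wording change and, for the first option, a different data layout in the same Stata procedure. Hospitalizations are already recorded at the regular household visits, so no new data item is proposed.
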